10.1 Handling and storage of data and documents

10.2 Amendments

10.3 Annual progress report

10.4 End of study report

11. REFERENCES

## **LIST OF ABBREVIATIONS AND RELEVANT DEFINITIONS**

ABR ABR form: (General Assessment and Registration form) is the application form that is required for submission to the accredited Ethics Committee (ABR = General Assessment and Registration)

AE: Adverse Event

AR: Adverse Reaction

CA: Competent Authority

CCMO: Central Committee on Research Involving Human Subjects

CV: Curriculum Vitae

DSMB: Data Safety Monitoring Board

EU: European Union

EudraCT: European drug regulatory affairs Clinical Trials GCP Good Clinical Practice

IB: Investigator's Brochure

IC: Informed Consent

IMP: Investigational Medicinal Product

IMPD: Investigational Medicinal Product Dossier

METC: Medical research ethics committee (MREC) in English: medical research ethics committee (METC)

(S) AE: Serious Adverse Event

SPC: Summary of Product Characteristics (in Dutch: official product information IB1 text)

Sponsor: The sponsor is the party that commissions the organization or performance of the research, for example a pharmaceutical company, academic hospital, scientific organization or investigator. A party that provides funding for a study but does not commission it is not regarded as the sponsor, but referred to as a subsidising party.

SUSAR: Suspected Unexpected Serious Adverse Reaction

DPA: Personal Data Protection Act (in Dutch: Person Protection Act Stat)

WMO: Medical Research Involving Human Subjects Act (Act Medical Research Involving Human

## SUMMARY

**Rationale:** High blood pressure (BP) is more prevalent and has more serious complications among migrants of African descent than among Dutch. In the treatment of hypertensive patients of African descent, less optimal blood pressure values are achieved than among the native Dutch hypertensive patients. Adherence to treatment is essential for achieving good blood pressure values and lowering of the cardiovascular risk profile. Adherence is generally low among hypertensive patients and in particular among patients from ethnic minority groups. Tailored patient education can promote adherence. The aim of this project is to evaluate a protocol for 'culture-sensitive education'(CAHE), which is meant to guide patients in implementing lifestyle changes and proper use of medication. The target group (of this educational intervention) consists of Afro-Surinamese and Ghanaian patients who are treated for BP in general practice. CAHE was developed through a bottom-up approach in two previous projects, namely 'Heebroedoe' and 'Under Pressure I (OHD1). In these projects, two groups participated: those for which the information is intended (Ghanaian and Surinamese BP-patients) and providers engaged in the promotion of healthy behavior among BP patients (GPs, practice nurses (POH-ers), center assistants and others). The protocol has been tested by center assistants and POH-ers in three health centers in Amsterdam South East (OHD1). This demonstrated that the protocol is well applicable, particularly by POH-ers. These professionals have extensive experience and training in providing patient education in general.

### **Objectives:**

Overall objective: To evaluate the effect of 'culturally-sensitive hypertension Education'(CAHE) in Afro-Surinamese and Ghanaian patients who are treated in general practice for high blood pressure and have a blood pressure above target (systolic blood pressure (SBP)> 140 mmHg and / or diastolic blood pressure (DBP)> 90 mmHg).

Primary specific objective:

1. To determine if there are significant differences in the reduction in systolic blood pressure between the intervention group (patients who have received CAHE) and the control group after eight months past baseline.

Secondary specific objectives:

2. To evaluate whether, whether there are significant differences in the degree of medication adherence between the intervention group (patients who have received CAHE) and the control group at 8 months past baseline.

3. Evaluate whether there are significant differences in the adherence to lifestyle advice between the intervention group (patients who have received CAHE) and the control group, at 8 months past baseline.

**Study design:** Randomized controlled trial, in which data will be collected at the level of the patient, and randomization takes place at the level of clusters (4 health centres);

Also, a process evaluation will be conducted to gain insight in factors that determine the observed effects of the intervention.

**Study population:** Hypertensive patients from primary care practice: Afro-Surinamese or Ghanaian (according to self-identification), > 20 years old, diagnosed with hypertension (K86, K87), systolic blood pressure > 140 mmHg and / or diastolic blood pressure > 90 mmHg. Patients are excluded if they have diabetes mellitus type 1 or 2 have, participate in other CVD trials, or if the treating physician deems participation to be inappropriate (eg because of existing comorbidities)

**Intervention (if applicable):** Patients in the intervention group will have three education meetings according to a protocol for culture-sensitive patient education (CAHE) with a trained POH, at an interval of three months. These patients also receive the usual guidance as provided in the health centers.

**Main study parameters / endpoints:** Primary outcome measure is the measured systolic blood pressure at baseline minus the systolic blood pressure after 8 months (blood pressure is electronically measured twice, for sitting patients after 15 minutes of rest, the average of the two measurements is recorded.). Secondary outcomes are changes after 8 months in the degree of adherence to medication and lifestyle advice; mediating factors that may influence how patients deal with hypertension: (beliefs about hypertension and medication / lifestyle changes, motivation for medication use and lifestyle changes, perceived self-efficacy to use medication/carry out lifestyle changes and satisfaction with care.

**Nature and Extent of the burden and risks associated with participation, benefit and group relatedness:**

1.

Patients will get a physical examination from research assistant (measurement of blood pressure, weight, height and waist circumference) and an interview. To determine the salt excretion at the interview patients will be asked to bring a tube of morning urine at T0

2.

Patients in the control group receive care as usual.

Patients in the intervention group will receive, in addition, three educational sessions according to a protocol for culture sensitive patient education from research nurse (three-month intervals: T1-T2-T3)

3.

In addition, in all patients BP will be measured three times and patients will be asked to fill out a brief self-report questionnaire on medication/life style compliance. (three-month intervals: T1-T2-T3)

4.

Finally, at the final measurement (post test), patients will get a physical examination (blood pressure measurement, weight, height and waist circumference) and an interview from a research assistant. To determine the salt excretion they will be asked to bring a tube of morning urine to the final interview (Posttest)

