After the T0 assessments, patients in the intervention group will receive three appointments for CAHE sessions with the POH (2 weeks, 3 ½ and 6 ½ months after T0 measurement) At these intervals the POH will also measure patients' BPs with an electronic device (Omron 705-IT) according to a standardized method, the treating POH. This is a standard component of hypertension education, both in the experimental intervention protocol and in the NHG protocol. At these points, we will also measure the self-reported adherence to medications and lifestyle advice through a short questionnaire. The POH will ask the patient to complete these lists in the waiting room.

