#### CONTROL GROUP

The POH's in control centers give patients the usual care. The patients in the control group will be given an appointment at 3 ½ and 6 ½ months after the T0 measurement to get their repeat prescriptions for anti-hypertensive medications. A blood pressure reading will be performed by the treating POH with an electronic device (Omron 705-IT) according to a

standardized method. In all patients in the control group after 3 ½ and 6 ½ months self-reported adherence to medication and lifestyle advice will be measures via a short questionnaire. The POH will ask the patient to complete these lists in the waiting room

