## **6. METHODS**

### **6.1 Study parameters / endpoints**

#### **6.1.1. Main study parameter / endpoint**

Difference between baseline systolic blood pressure and systolic blood pressure at 8 months past baseline.

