#### **Blinding**

In order to ensure blinding the measurements will be carried out as follows:

1. For the purpose of the beginning (T0) and the final measurement a research nurse will blood pressure measurements and physical examinations in all participating health care centers and collect the batch of morning urine from the patients. For blood pressure measurements validated electronic devices will be used (Omron 705-IT). A research assistant will carry out the study's questionnaire to assess other outcome measures. The research nurse and research assistant will be blinded to the study arms to which centers are allocated..
2. In the two intervention centers a POH will be responsible for delivering CAHE. The POH will receive a clear protocol and training (see 5.1). S/he will also be instructed to provide no

information about the study or the patient education to colleagues. The POH's in control centers will give patients the usual care. The blood pressure measurement is a standard component of hypertension education, both in the intervention and usual care. The interim blood pressure measurements at 3, 6 and 9 months, will be carried out by the attending POH's with the above-described electronic devices. The use of a standardized measurement methods restricts the possibility of ascertainment bias.

3. There will be blinding during while entering and analyzing the data. All data from the intervention and control groups are stored in one data set and the researchers who are cleaning the data will be blinded to the study arms.

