##### *Pre and post-test*

Patients in the intervention group and the control group will participate in a series of pre- and a post-intervention measurements which will be conducted by a specially trained research nurse. Baseline measurements will take place as soon as possible (within two weeks) after inclusion and final measurements between four-to-six weeks after the patients' last educational session/ repeat prescription. All the measurements will be carried out in one of the four health care centers that participate in the study and, if possible, the health care center where the patient is registered. The measurement consists of: 1. A physical examination, 2. Identification of additional risk factors for CVD and 3. the administration of a questionnaire.

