#### *T1-T2-T3 measurement*

After the physical examination for the T0 assesment, three appointment will be made with patients in the intervention for the three CAHE sessions. A first after 2 weeks and on two subsequent times (intervals of 3 months).

After each session in patients in the intervention group blood pressure measurements performed by the treating POH (T1), (T2) (T3). In patients in the control group BP measurements will be conducted (after 3 ½ and 6 ½ months) by their treating POH in a standardized manner. On those occasions self-reported adherence to medication / lifestyle advice will also be measured with the Morisky scale and adapted Morisky scale, respectively. The treating POH will ask the patient to fill in this list in the waiting room

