### **8.1 Descriptive statistics**

Quantitative data: Primary outcome measure: The main purpose of this study is to measure the effect of the intervention on systolic blood pressure in mmHg (difference between systolic blood pressure (SBP) measured at baseline and after 8 months)

Qualitative data: For a better understanding of the effects of the intervention a process evaluation was carried out, on the basis of the aforementioned qualitative data. This data will be transcribed in whole or in part. The analysis will be carried out using the computer analysis program MAXQDA, based on predefined questions and codes (framework analysis): topics that are addressed in intervention sessions; barriers that arise in these sessions; factors impeding or promoting adherence to medication and lifestyle advice; explanatory model of hypertension. Data on the number and reasons for refusals to participate in CAHE sessions or to terminate these sessions will be analyzed for frequency and content.

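### The final systolic pressure is timed from the last session or repeat prescription instead of 8 months from baseline, so a postponed contact moves the primary outcome; the interim schedule also needs a minor correction

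*Protocol*

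**What the plan says.** **Endpoint.** Section 6.1.1 defines the primary outcome as "Difference between baseline systolic blood pressure and systolic blood pressure at 8 months past baseline". The Summary and Sections 2, 8.1 and 8.2 give the same 8 months.

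**Timing of the final visit.** Section 6.3 (Pre and post-test) places the "final measurements between four-to-six weeks after the patients" last contact. That contact is an education session (CAHE) in the intervention arm and a repeat prescription in the control arm. The section does not express the visit in months from T0.

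**Interim contacts, detailed sections.** Section 5.1 gives intervention patients "three appointments for CAHE sessions with the POH (2 weeks, 3 ½ and 6 ½ months after T0 measurement"). For control it says "The patients in the control group will be given an appointment at 3 ½ and 6 ½ months after the T0 measurement", and Section 6.3 (T1-T2-T3 measurement) agrees: "In patients in the control group BP measurements will be conducted (after 3 ½ and 6 ½ months) by their treating POH".

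**Interim contacts, other places.** Item 3 of the burden paragraph in the Summary says that "in all patients BP will be measured three times and patients will be asked to fill out a brief self-report questionnaire", at T1, T2 and T3. Section 6.2 (Blinding) says: "The interim blood pressure measurements at 3, 6 and 9 months, will be carried out by the attending" practice nurses, without distinguishing the arms.

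**Incomplete attendance.** Section 8.1 foresees it: "Data on the number and reasons for refusals to participate in CAHE sessions or to terminate these sessions will be analyzed". Section 6.1.3 also records reasons for stopping scheduled consultations in the study arms. Section 8.2 analyses the primary outcome by intention to treat.

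**The concern.** The endpoint is defined by time since baseline, but the visit that produces it is timed from something that happens after randomisation. The two agree only if the 6½-month contact takes place on time.

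The reference event also differs by arm: a session of the experimental education in one, a prescription renewal in the other. If these are postponed to a different extent, the arms are measured at different times since baseline, and part of the difference in SBP change could reflect time rather than education. Under intention to treat, a patient who delays or stops sessions still needs a reading at the same nominal time as everyone else.

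The interim schedule is a separate and smaller matter. A control centre cannot tell from the protocol whether to take two readings or three, and an interim reading at 9 months would fall after the 8-month final one.

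**Working it through.** **Inputs.** Contacts at 2 weeks (intervention only), 3½ and 6½ months from T0 (Section 5.1); final visit 4 to 6 weeks, that is 28 to 42 days, after the last contact (Section 6.3); endpoint at 8 months (Section 6.1.1). One month is taken as 30.44 days. The slips of 1 and 2 months are assumptions for illustration; the protocol gives no figure for delays.

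**Formula.** Final visit in months = (day of last contact + 28 to 42) / 30.44.

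**The plan's own schedule first.** 6.5 × 30.44 = 197.9 days. Adding 28 to 42 gives days 225.9-239.9, or 7.42-7.88 months, in both arms. This is close to the stated 8 months.

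**Departures from schedule.**

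| Last contact | Day | Final visit (days) | Final visit (months) | Arms |
|---|---|---|---|---|
| 6½ months, 1 month late (assumed) | 228.3 | 256.3-270.3 | 8.42-8.88 | either |
| 6½ months, 2 months late (assumed) | 258.7 | 286.7-300.7 | 9.42-9.88 | either |
| 3½ months, if *last* means last attended | 106.5 | 134.5-148.5 | 4.42-4.88 | either |
| 2 weeks, if *last* means last attended | 14 | 42-56 | 1.38-1.84 | intervention only |

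The first two rows need only a postponed contact. The last two also need the last-attended reading. Under that reading, a patient who attends no session has no final visit date at all.

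**A window from T0.** 8 × 30.44 = 243.5 days. ±21 days gives days 222.5-264.5, or 7.31-8.69 months. This contains the planned 7.42-7.88 months.

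**Interval from last session to final reading under that window.**
- On time (day 197.9): 222.5 − 197.9 = 24.6 days to 264.5 − 197.9 = 66.6 days, about 3.5 to 9.5 weeks, against 4 to 6 weeks now.
- One month late (day 228.3): from 5.8 days (0.8 weeks) before session 3 to 36.2 days (5.2 weeks) after it.
- Two months late (day 258.7): from 36.2 days (5.2 weeks) before session 3 to 5.8 days (0.8 weeks) after it.

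**Interim schedule, side by side.**

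| Place | Intervention | Control |
|---|---|---|
| Summary, burden item 3 | 3 readings | 3 readings |
| Section 6.2 | 3, 6, 9 months | 3, 6, 9 months |
| Sections 5.1 and 6.3 | 2 weeks, 3½, 6½ months | 3½, 6½ months |

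Only the last row leads to a final visit near 8 months. If a 9-month contact were the reference, the same formula would give 9.92-10.38 months. The Summary and Section 6.2 are therefore the places to correct.

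**The case against.** **Meaning of *last*.** The strongest reply is that there are exactly three sessions, appointments for all three are made after T0, and *last* can naturally mean the third scheduled one (for control, the 6½-month prescription appointment). Early stoppers and non-attenders would then still be due at 7.4-7.9 months. This stands. A reader might infer that the protocol does measure early stoppers at 1.4-1.8 or 4.4-4.9 months; the text does not establish that, only that it is one possible reading. The reply does not cover postponement: even on the scheduled-session reading, a delayed third session delays the final SBP.

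**Dropout.** A reader might take the 50% dropout in Section 4.4 as the share of patients with a mistimed reading. It is not. It inflates 120 patients to 240 recruited, so it allows for patients without a usable outcome. Sections 6.1.3 and 8.1 show that stopping is expected, but give no rate.

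**Visit windows belong elsewhere.** Windows and the handling of off-schedule readings are commonly left to an analysis plan, so a missing window is not in itself a fault. The event from which the visit is timed, however, is stated in the protocol, and it does not match the endpoint.

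**The interim contradiction is editorial.** This also stands. Sections 6.1.1 and 6.1.2 define the primary and secondary outcomes as change from baseline to 8 months, so none uses the interim readings. A reader might infer that the contradictory schedule disturbs the primary outcome; it does not.

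**Conclusion.** The point holds in limited form. With on-time contacts the rule in Section 6.3 gives 7.4-7.9 months in both arms and the primary outcome is not disturbed. When the third session or repeat prescription is postponed, the final SBP leaves the stated 8 months by about as much as the slip, whichever way *last* is read. The shift can differ by arm because the reference events differ. Measurement at 1.4-1.8 or 4.4-4.9 months depends on the last-attended reading, which is not settled.

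The protocol gives no rate of delayed or stopped sessions, so neither the number of patients affected nor a bias in mmHg can be computed, and none is claimed. The case for change is that outcome timing should not depend on post-randomisation behaviour when timing from T0 is just as easy. The contradictory interim schedule is real but is only a consistency correction.

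**What to change.** 1. **Section 6.3 (Pre and post-test).** Schedule the final measurement at 8 months from T0 in both arms, with the same window, whether or not the sessions or repeat prescriptions were completed. A window of ±3 weeks (7.3-8.7 months) is one suitable choice.
2. **Summary, burden item 3.** State three interim contacts in the intervention arm and two in control.
3. **Section 6.2 (Blinding).** Replace the 3-, 6- and 9-month times with 2 weeks (intervention only), 3½ and 6½ months, to match Sections 5.1 and 6.3.

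**Cost.** Wording in three places and no added visits; on-schedule patients already fall inside the example window. The price is a less uniform interval between last session and final SBP (about 3.5-9.5 weeks when on time). A patient whose third session slips by 1 to 2 months may also be measured before that session. This is acceptable under intention to treat, but the sponsor should accept it knowingly.

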## 1. INTRODUCTION

High blood pressure (BP) is a major risk factor for cardiovascular disease (CVD). In BP patients this risk can be reduced through lifestyle changes that reduce additional risk factors for CVD reduction (smoking cessation, regular exercise, healthy diet, moderate alcohol consumption and reducing obesity) and if needed through proper medication use. (1) In Western countries the prevalence of BP is higher among people of African origin than among white populations. (2) According to the SUNSET study in the Netherlands the prevalence is 2 and 4 times, higher among African-Surinamese men and women than among Dutch men and women respectively. (3) Also high prevalences of hypertension and malignant hypertension were found among Ghanaians. (4-5) The SUNSET study found that only 14% of African-Surinamese men and 49% of African-Surinamese women in treatment for BP, had a blood pressure below the target values. A significant part of those who were treated also had additional risk factors for CVD: Overweight, obesity, smoking, and physical inactivity (6) Among patients with BP adherence to lifestyle advice and medication is moderate (7-9) There are indications that this is even lower in ethnic minority groups, among other reasons because of cultural perceptions and practices that lead to people own medication practices and difficult communication between staff and patients. (10-14) A poorly controlled blood pressure and an unhealthy lifestyle can lead to unnecessary health damage and death. This damage can be prevented with better guidance. The GP plays a central role in the diagnosis and treatment of BP. (15) The NHG Standard Cardiovascular risk management (CVRM) considers education and advice as the main instruments for guiding patients towards changes in lifestyle and medication use. (1) Various studies have shown that the effect of education is increases the better it is tailored to the perspective, the needs and abilities of the patient. (7, 16-18) At the same time "culture-sensitive" information ( CAHE) seems to have a positive effect among ethnic minority groups. (19) The recommended method for patient education in the NHG standard CVRM (the schedule of the 5 A's) does not differentiate according ethnicity. (20) The primary health centers in Amsterdam Southeast, have many patients of African descent, particularly Afro-Surinamese and Ghanaians, which is consistent with the demographic characteristics of this region. Many of these centers utilize a common protocol for the treatment and education of patients with BP, which is based on the NHG standard CVRM. In an earlier study, we examined in Ghanaian, African-Surinamese and Dutch patients from three of these health centers if cultural perceptions play a role the way they deal hypertension and, if so, whether the existing education methods must be adapted. Based on the results, (21-25) and recommendations, (26) in a follow-up project we complemented the existing CVRM protocol (and digitized) with recommendations for culture-sensitive hypertension education (26) The annexes to the protocol also contain newly developed information materials on BP management and diet for Ghanaian and Afro-Surinamese BP patients. It also contains map with existing health promotion activities aimed at these groups in the area that can be used to refer patients. By means of pilot the revised protocol has been used for 6-8 months by POHers and CAs of three health care centers. Health care providers evaluated their experiences with implementing the protocol is. This showed that it is suitable for use in practice and in particular by POH-ers.

The present study aims to take a further step by evaluating the effect of CAGE in Afro-Surinamese and Ghanaian patients with hypertension. By means of an intervention, the protocol for CAHE will be delivered by a specially trained POH. This POH will conduct three CAHE sessions with patients with an interval of three months. The intervention will tested in a study with a cluster randomized controlled design. It is hypothesized that, through cultural tailoring, the effectiveness of the education will increase,

We expect that the intervention will have a positive effect on the systolic blood pressure and and the degree compliance to medications and lifestyle advice and on some mediating factors that affect patients' management hypertension. This way, the project hopes to contribute to reducing ethnic differences in blood pressure control and health outcomes in people with BP (particularly those of African descent)

